## Abstract

**Introduction::**

Currently, none of the available multiple sclerosis (MS) disease-modifying medications has been shown to stop or reverse gait disability. Recently, the nabiximols has been tested for the treatment of spasticity and walking impairment in MS. Nabiximols (trade name Sativex) is an oromucosal spray formulation containing 1:1 fixed ratio of delta-9-tetrahydrocannabinol and cannabidiol derived from cloned Cannabis sativa L. plant.

**Method and analysis::**

A single-center, prospective, parallel design, single-blind trial will be conducted at the IRCCS Neurolesi “Bonino-Pulejo” (Italy) involving MS patients affected by spasticity and undergoing a Robotic Rehabilitation training. The aim of the study is to clarify the role of Sativex coupled to a robotic neurehabilitation training in MS patients in improving motor outcomes, by means of clinical, kinematic, and neurophysiological measures. Patients will be randomly divided in 2 groups: one taking only an oral antispastic drug and the other with Sativex in add-on. After 1 month, we will evaluate the response to Sativex (responder patients’ amelioration >20% at MRS score) enrolling into the study the first 20 patients with a good response to Sativex, whereas other 20 no-responder individuals will continue their antispastic drug. All the 40 subjects, were divided into 2 groups (A: Sativex + Lokomat Training, and B: other antispastic+Lokomat Training), will perform a neurorobotic-assisted gait training (each session will last at least 45 minutes, 3 times per week, for a total of 20 sessions). All the patients will undergo a complete physical and neurological examination at baseline, at the end of the robotic training (T1), and 30 days after the end of the neurorehabilitation training (T2).

## Introduction

1

### Background and rationale

1.1

Multiple sclerosis (MS) is the second most common cause of neurological disability in adults between 18 and 50 years of age. Gait, coordination, and balance are affected even in people with only mild neurological signs. ^[1]^ Moreover, after early walking problems have been detected, time until complete loss of independent ambulation is predictable, regardless of the relapsing or progressive onset. Spasticity is frequently experienced by people with MS, negatively affecting patient's motor functional outcome, including walking.^[2]^ Currently, none of the available MS disease-modifying medications has been shown to stop or reverse gait disability. Recently, the nabiximols has been tested for the treatment of spasticity and walking impairment in MS. Nabiximols (trade name Sativex) is an oromucosal spray formulation containing 1:1 fixed ratio of delta-9-tetrahydrocannabinol (THC) and cannabidiol (CBD) derived from cloned *Cannabis sativa L.* plant. The main active substance, THC, acts as a partial agonist at human cannabinoid receptors (CB_1_ and CB_2_), and may modulate the effects of excitatory (glutamate [GLU]) and inhibitory (gamma-aminobutyric acid [GABA]) neurotransmitters, leading to muscle relaxation, which in turn is responsible for spasticity improvement.^[3]^ The last 2 decades have seen a remarkable shift of therapeutic approach toward the neurorehabilitation paradigm, considering plasticity as a fundamental property of the human brain. In particular, gait robotic-rehabilitation (RAGT), with or without body weight support (BWS), may offer advantages beyond overground training, in terms of patient safety, reduced fear of falling, more steps practiced, repeatability, and less fatiguing motor paradigms. However, the current data in literature about the efficacy of neurorobotic training in MS are conflicting,^[4]^ although it has been hypothesized that virtual reality may strengthen RAGT thanks to the entrainment of different brain areas involved in motor planning and learning.^[5]^

Nevertheless, the neurorehabilitation plays a key role in preserving the neural-plasticity mechanisms. Cortical reorganization represents the expression of neuronal plastic changes that follow brain tissue damage in MS. Adaptive plasticity is suggested to maintain the expression of pathology at a subclinical level.^[6]^ However, cannabinoid receptors may modulate both excitatory and inhibitory transmission at central synapses, and have been heavily implicated in multiple forms of synaptic plasticity, such as long-term potentiation (LTP) and long-term depression (LTD).^[7]^ Indeed, in a previous study implying transcranial magnetic stimulation (TMS) technique, Koch et al^[8]^ hypothesized that the activation of cannabinoid receptors by Sativex could modulate the balance between LTP and LTD like plasticity by changing the state of cortical excitability. Recently it has been suggested that Sativex may modulate the cortical excitability by changing the activity of the inhibitory GABAergic cortico-cortical synapses.^[3]^

## Objectives

2

Aim of the study is to clarify the role of Sativex coupled to a robotic neurehabilitation training in improving motor outcomes, by means of clinical, kinematic, and neurophysiological measures in patients with MS affected by spasticity.

## Methods

3

### Trial design

3.1

This is a rater-blinded, active-controlled, parallel-group pilot study to assess the efficacy of Sativex associated with robotic-rehabilitation in improving the motor performances of Multiple Sclerosis patients. This study will be conducted at the IRCCS Centro Neurolesi Bonino-Pulejo in Messina, Italy. The study protocol was approved by the Ethical and Research Committee of IRCCS Centro Neurolesi Bonino-Pulejo (13/2016 vers, n 1 23/11/2016). The trial is registered under trial gov. (NCT03186664). The study purpose will be explained to the participants, and patients’ consent will be obtained before the enrollment by the principle investigator.

### Eligibility criteria

3.2

We will enroll 40 MS patients affected by gait disturbances and moderate-severe spasticity: 20 of them in treatment with Sativex (Group A) considered as responders, and 20 treated only with the most common antispastics used in MS (Group B). Inclusion criteria are: age range 18 to 65 years; diagnosis of definite relapsing-remitting or primary-progressive or secondary-progressive multiple sclerosis; absence of clinical relapses from no gadolinium-enhanced lesions on brain and spinal cord MRI performed at least 6 months before study entry; no mood or sleep disorders with an Hamilton score of ≤17; a moderate to severe spasticity in at least 2 districts of upper and/or lower limbs; absence of clinical or neuroradiological relapses from at least 6 months before study entry; Expanded Disability Status Scale (EDSS) total score between 3.5 and 7.0; no history of psychosis; no presence of pace-maker, aneurysms clips, neurostimulator or brain/subdural electrodes (safety TMS procedure); right handedness, central conduction time in upper limbs of <8 ms; no robotic gait training contraindications.

### Exclusion criteria

3.3

We consider as exclusion criteria the following: history of psychosis, presence of pace-maker, aneurysms clips, neurostimulator or brain/subdural electrodes (safety TMS procedure), central conduction time in upper limbs of <8 ms; RAGT contraindications.

### Prescreening

3.4

We evaluated 90 MS patients attending the tertiary MS Center of the IRCCS “Bonino-Pulejo” with a moderate to severe spasticity despite oral antispastic treatment (i.e., Baclofen) and a gait disturbance. We randomly divided the population in 2 groups: one with the same oral therapy and the second with Sativex in add-on. After 1 month, we evaluated the response to Sativex (responder patients’ amelioration >20% at MRS score). We included into the study the first 20 patient responders to Sativex and 20 who continued their ongoing antispastic treatment.

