### Study population

3.6

All the 40 subjects, divided into 2 groups (A: Sativex + Lokomat Training, and B: other antispastics + Lokomat training) will perform a RAGT (each session will last at least 45 minutes, 3 times per week, for a total of 20 sessions).

All the patients will undergo a complete physical and neurological examination, including the evaluation of disability by means of the EDSS, the assessment of spasticity using the Modified Ashworth Scale (MAS), and the numerical rating scale (NRS). To clarify the role of Sativex in improving spasticity gait-related symptoms, we will also administer the following scales: 10 meters walking test (10WT) and Ambulation Index (AI). Quality of life will be evaluated by means of MS quality of life 54 (MSQOL-54). The skilled clinician will be blind to the drug treatment. Moreover, we will evaluate some electrophysiological parameters to test cortical excitability: motor-evoked potentials (MEP) amplitude, short intracortical inhibition (SICI) and facilitation (ICF) from the abductor pollicis brevis muscle (APB) of the most affected side. The same assessment will be applied at baseline, at the end of the RAGT (T1), and 30 days after the end of the neurorehabilitation training (T2).

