#### Visit 1 (baseline)

3.11.2

Medical history with particular regard to antispastic drug intake. FIM, MAs, NRS, 10mW, 6MW, HRSD, and MSQOL 54. Muscular stiffness and strength will be evaluated by means of instrumental measures furnished by the neurorobotic device itself. Neurophysiological measure will be also assessed.

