### Statistical analysis

3.13

The Wilcoxon signed ranks test on the T0-T1-T2 differences concerning the different clinical outcome measures (EDSS, FIM, MAs, 10mW, 6MW, HSD, MSQOL 54) will be carried out in both groups. The α-level for significance will be set at *P* < 0.05. The Bonferroni correction will be used in multiple comparisons. Data will be expressed as mean or percentage ± standard deviation. The effects of the treatment on RMT, peak-to-peak MEP amplitude, SICI, and ICF will be evaluated in separate repeated-measures analyses of variance (rmANOVA). For each dependent variable, we will compute a 2-way rmANOVA with time (4 levels: T_0_- T_1_-T_2_) and group (2 levels: group A and group B) as within-subject factors. Conditional on a significant F value, post-hoc paired-sample *t* tests were performed to explore the strength of main effects and the patterns of interaction between experimental factors. The Greenhouse-Geisser method will be used if necessary to correct for nonsphericity. All data will be given as means or percent ± standard error. We also will calculate a Fisher Z-transformation concerning the correlations between clinical and electrophysiological parameters.

This is a pilot study. The main aim is to provide evidence which could allow planning of a further confirmatory study. The simple size of 40 patients was determined on the basis of feasibility criteria. Consequently, no formal statistical hypothesis was done

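### By the order of events, T0 falls after a month of Sativex and responder selection in Group A, so T0-T1-T2 changes describe the training phase in responders, not the effect of adding Sativex

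*Protocol article*

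**What the plan says.** All references are to the protocol article.

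- **Prescreening (3.4), allocation:** "We randomly divided the population in 2 groups: one with the same oral therapy and the second with Sativex in add-on".
- **Prescreening, response check:** "After 1 month, we evaluated the response to Sativex", where response means more than 20% improvement on the spasticity score.
- **Prescreening, entry:** "We included into the study the first 20 patient responders to Sativex and 20 who continued their ongoing antispastic treatment". Eligibility criteria (3.2) agree, since Group A is enrolled already on Sativex and counted as responders.
- **Abstract, Group B:** described differently, "whereas other 20 no-responder individuals will continue their antispastic drug".
- **Participants Timeline (3.11):** the pre-screening visit lists criteria and consent only. Visit 1 (baseline) follows, with the outcome battery and "Medical history with particular regard to antispastic drug intake".
- **Study population (3.6):** the same assessment is made "at baseline, at the end of the RAGT (T1), and 30 days after the end of the neurorehabilitation training (T2").
- **Statistical analysis (3.13):** "The Wilcoxon signed ranks test on the T0-T1-T2 differences concerning the different clinical outcome measures", run in each group. The TMS measures go into repeated-measures ANOVAs by time and group. Time is given four levels, but only T0, T1 and T2 are named. The Sample size section (3.12) also counts four measurements.

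**The concern.** A baseline is normally read before the treatment being compared has started. Here the order of events makes T0 a post-randomisation value. It is on-drug in Group A, off-drug in Group B, and in Group A it follows selection for a recent improvement.

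The trial design section sets out to assess the efficacy of Sativex combined with robotic training, and the study population section says the gait scales are there to clarify what Sativex does for gait-related spasticity symptoms. A change measured from T0 cannot show a benefit that had already arrived by T0. If most of the drug's benefit comes in the first month, the T0-based changes could look alike in both groups although the drug works. The trial is a pilot meant to inform a confirmatory study, so a misread estimate would carry forward into that design.

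Selection raises a second, conditional worry. If the reading that qualified patients as responders also serves as T0, it will on average be too low, and later readings will rise for no clinical reason.

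**Working it through.** **Step 1. Place T0 in the sequence.** From sections 3.2, 3.4, 3.6 and 3.11:

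1. randomisation of 90 patients;
2. one month of add-on Sativex or unchanged therapy;
3. response check;
4. inclusion of 20 + 20 patients;
5. baseline visit (T0);
6. training;
7. T1;
8. T2, 30 days later.

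The position of T0 is inferred from this order. The undefined fourth time level leaves room for a pre-drug reading that the article does not describe.

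**Step 2. What the planned changes contain.** Write D1 for the drug effect reached by T0 and D2 for any further effect during training. For Group A:

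- change from before the drug to T1 = D1 + D2 + training gain
- change from T0 to T1 = D2 + training gain

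D1 drops out of every T0-based change, whatever its size. The same holds for the group-by-time interaction in the TMS models. A group main effect there would contain D1, but mixed with responder selection. This step needs no numerical assumption.

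**Step 3. Size of the conditional drift.** The document gives no mean, SD or reliability for the selection score, so all of these inputs are assumed: 0-10 score, pre-drug mean 6.5, SD 1.5, single-visit reliability 0.7, true drug effect -1 point in everyone, visit errors independent, no training effect. Select patients with (pre - 1-month)/pre > 0.20. Simulation of 400,000 patients gives, among those selected:

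| Reading | Mean |
|---|---|
| Pre-drug | 6.71 |
| 1-month selection reading | 4.60 |
| T1 | 5.21 |

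- If T0 is the selection reading: T1 - T0 = 5.21 - 4.60 = +0.61, an apparent worsening with no real change.
- If T0 is a fresh reading after selection, its mean equals that at T1, and the drift is 0.00.
- Range when T0 is the selection reading: +0.45 (mean 6.5, reliability 0.85) to +0.73 (mean 7, reliability 0.6).

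**Step 4. Split the observed first-month fall.** The observed fall is 4.60 - 6.71 = -2.11. The true pre-drug mean of those selected is 5.21 + 1.00 = 6.21. The fall therefore splits as follows:

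- drug effect: -1.00
- pre-drug reading too high by chance: 6.21 - 6.71 = -0.50
- selection reading too low by chance: 4.60 - 5.21 = -0.61
- sum: -2.11

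**Step 5. Does a pre-drug baseline cure it in the enrolled patients?** No. Pre-drug to T1 is 5.21 - 6.71 = -1.50 against a true -1.00, so the effect is overstated by half. With no drug effect at all, the same contrast in selected patients is about -0.84. In all patients randomised to Sativex, with no selection, the pre-drug to 1-month change averages the true effect.

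**The case against.** The strongest reply is that T0 is a sensible start. The objective is Sativex coupled to training, and the discussion speaks of boosting the Lokomat effect. For that question, change from the start of training is the natural measure. This stands: T0-to-T1 is a legitimate contrast, provided it is labelled as such. It does not cover the article's wider statements about the efficacy and role of Sativex. Calling the study a pilot without a formal hypothesis lowers the stakes but does not change what the contrast measures.

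A reader might infer several stronger claims that the document does not support:

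- **That the T0-T1-T2 changes certainly carry regression to the mean.** This needs T0 to be the selection reading or to share its visit-level error. The article lists a response check and a separate baseline visit, and does not say whether they coincide.
- **That the 0.6-point drift sits in a planned clinical test.** The selection score (printed as MRS, probably the NRS) is not in the list of scales for the Wilcoxon tests. Other scales are affected only through shared visit-level error, and nothing in the document quantifies that.
- **That only one arm is selected.** Prescreening gives no response rule for Group B, but the abstract calls those patients non-responders. If they were selected on non-response to Sativex, and T0 reused that reading, their score would drift down. Under a second set of assumed inputs (mean 7, reliability 0.5 to 0.9, effect 0 to 1.5 points) the drift is -0.02 to -0.60 points.
- **That no pre-drug value enters any analysis.** The undefined fourth time level prevents so firm a statement.
- **That T0 as a covariate would adjust away the effect.** The article describes no covariate model, and its only between-group models are for TMS outcomes.

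**Conclusion.** The point holds in a limited form. On the order of events in the article, T0 comes after randomisation, a month of Sativex and responder selection in Group A. Changes from T0 therefore exclude any drug effect gained in the first month and describe the training phase in Sativex responders. This rests on the visit sequence rather than a stated date, but no other order fits the eligibility and prescreening sections together.

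The drift against Sativex is conditional: +0.45 to +0.73 points on the selection score if T0 reuses the selection reading, zero if it does not, under assumed reliability 0.6 to 0.85 and a true effect of -1 point. Simply moving the baseline back to the pre-drug value in the enrolled patients would replace the omission with a bias toward Sativex (about -1.5 observed against -1 true), because selection on response remains. The matter should be corrected. It does not invalidate the training-phase comparison as a description.

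**What to change.** 1. State when T0 is taken relative to the start of Sativex, and make it a reading separate from the 1-month response check. If the baseline has already been taken, state which reading was used.
2. Label T0-to-T1 and T0-to-T2 contrasts as training-phase change, in Group A among Sativex responders, and limit the conclusion to that.
3. For measures with a pre-randomisation value (at least the score behind the 20% rule, which cannot be applied without one), also report change from that value:
   - for all randomised patients, by assigned arm, up to the 1-month check;
   - to T1 in the enrolled 40, only with a statement that responder selection inflates it in favour of Sativex.
4. Reconcile the abstract and Prescreening on how Group B was chosen.
5. Define the fourth time level, or correct it to three in both the sample size and statistical analysis sections.

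The cost is a little more analysis and a narrower stated conclusion. The by-arm report to 1 month needs the response-check score for both randomised groups; if it was recorded only under Sativex, that should be said. Scales with no pre-randomisation value keep T0 as their only baseline, stated as a limitation.

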### Randomization of participants

3.5

The subjects were randomly assigned to one of the two treatment groups, using a simple randomization scheme generated by a software (www.randomization.com). Individual, sequentially numbered index cards with the random assignments were prepared. The index cards were folded, and placed in sealed opaque envelopes

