## Discussion

4

Spasticity is frequently experienced by individuals with MS, negatively affecting patient's functional outcomes.^[2]^ A previous study showed that Sativex is an effective add on option for moderate to severe spasticity in MS patients resistant to existing therapies, as demonstrated by its capability to improve spasticity and been evaluated by Visual Analog Scale and MAS scores.^[10]^ Sativex could be effective thanks to a double effect on intracortical and spinal plasticity modulating the balance between excitatory and inhibitory neurotransmitters.^[3]^ Cannabinoid receptors may modulate both excitatory transmission and inhibitory transmission at central synapses and have been heavily implicated in multiple forms of synaptic plasticity, such LTP and LTD.^[11]^ The RAGT offers many advantages in terms of patient safety, reduced fear of falling, number of steps practiced (intensity of the training), repeatability, and motor paradigm-induced fatigue as compared with the traditional over-ground training and/or treadmill with or without BWS in MS patients.^[12]^ Moreover, Lokomat optimizes sensory inputs that are relevant to step training, repeated practice, and neuroplasticity. A recent study showed that Lokomat training is effective in reducing reflex and intrinsic stiffness (which abnormally increase in spinal cord injury) and improving the abnormal modulation of reflexes over the ankle range-of-motion.^[13]^ There is growing evidence that the association between RAGT and specific antispastic therapy (as Tizanidine) is effective in improving training speed in people with spinal cord injury as compared to Lokomat alone.^[14]^

Keeping in mind all of these factors, a randomized trial was planned among MS patients that experienced spasticity and gait disturbance to investigate the role of Sativex in boosting the Lokomat effect. In relation to the capability of Sativex in modulating cortical plasticity,^[3]^ we can hypothesize that it can improve functional outcome and strengthen RAGT in effectively improving gait, balance.

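### Only the Sativex arm is filtered on one-month response after randomisation, so the 40-patient A-versus-B comparison is not randomised, and Group B is defined in two ways

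*Protocol article*

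**What the plan says.** All references are to the protocol article.

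- **Section 3.4, Prescreening.** The pool is 90 patients ("We evaluated 90 MS patients attending the tertiary MS Center"). Allocation comes first: "We randomly divided the population in 2 groups: one with the same oral therapy and the second with Sativex in add-on". The assessment follows: "After 1 month, we evaluated the response to Sativex", with response defined as "amelioration >20% at MRS score". Selection comes last: "We included into the study the first 20 patient responders to Sativex and 20 who continued their ongoing antispastic treatment".
- **Section 3.2, Eligibility criteria.** Agrees with 3.4: Group A are Sativex responders, and Group B are patients on common antispastics with no response condition.
- **Abstract, Method and analysis.** Describes the second group differently: "enrolling into the study the first 20 patients with a good response to Sativex, whereas other 20 no-responder individuals will continue their antispastic drug".
- **Section 3.5, Randomization of participants.** "The subjects were randomly assigned to one of the two treatment groups".
- **Section 4, Discussion.** "a randomized trial was planned among MS patients that experienced spasticity and gait disturbance", with the aim of finding out whether Sativex boosts the Lokomat effect.
- **Section 3.13, Statistical analysis.** Clinical scales are tested with Wilcoxon signed ranks tests in both groups. RMT, MEP amplitude, SICI and ICF are tested by rmANOVA with time and group (A, B) as factors. No allowance for the selection is stated.

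**The concern.** Randomisation makes two arms comparable at the moment of allocation. Here patients are then kept or dropped according to something observed a month later, in one arm only. A one-month improvement above 20% mixes drug effect, placebo response, natural fluctuation and measurement error. Keeping only improvers in Group A, with no matching condition in Group B, selects patients who may differ from controls in prognosis or changeability even if Sativex does nothing.

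A difference between A and B could then be read as Sativex strengthening the robotic training when it comes from the way Group A was assembled. Section 3.13 says the pilot is meant to supply evidence for planning a confirmatory study, so a selection-driven difference would pass into that plan.

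**Working it through.** **1. Order of events.** Section 3.4 gives: random division of 90, one month of treatment, assessment of response to Sativex, selection of 20 and 20. The filter therefore follows randomisation and applies to one arm. Section 3.5 could be read as a second randomisation of the 40, but that is impossible: Group A consists by definition of patients already on Sativex who responded to it.

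**2. Definition of Group B.** Sections 3.2 and 3.4 set no response condition; the Abstract makes the other 20 non-responders. It does not say to what they failed to respond. These are different populations, and the second makes the contrast with Group A more extreme.

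**3. Size of the selection effect.** The plan gives no figure for this; its sample size statement in 3.12 does not bear on it. Inputs:

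- From the documents: 90 patients, two arms, 20 selected per group, threshold 20%, alpha 0.05.
- Assumed: two-sided test; about 45 per arm (90/2; arm sizes are not given); responder share p of 44% (20/45 = 0.44, the share that just fills the quota) or 50%; correlation r between one-month percentage improvement and the later outcome of 0.2 to 0.7; outcome SD 1; no drug effect.

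Under normality, with k the upper-p point and φ the normal density, the expected spurious difference is

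- against unselected controls: r × φ(k)/p;
- against non-responders in the control arm: r × [φ(k)/p + φ(k)/(1−p)].

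For p = 0.44, φ(k)/p = 0.896 and φ(k)/(1−p) = 0.704. At r = 0.5 this gives 0.5 × 0.896 = 0.45 SD and 0.5 × 1.600 = 0.80 SD. For p = 0.50 both terms are 0.798, giving 0.40 and 0.80 SD.

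Simulation (2,000 runs per setting; first 20 eligible per group, or all if fewer; t test) gave:

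| r | Difference, B unselected (SD) | Type I error | Difference, B non-responders (SD) | Type I error |
|---|---|---|---|---|
| 0.2 | 0.17–0.19 | 7–8% | 0.32–0.33 | 16–17% |
| 0.3 | 0.25–0.27 | 12% | 0.47–0.48 | 31–34% |
| 0.5 | 0.39–0.45 | 23–29% | 0.80 | 74% |
| 0.7 | 0.55–0.63 | 44–54% | 1.12 | 98–99% |

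Taking the first 20 of each arm regardless of response gave differences of −0.02 to +0.02 SD and type I error of 4.1% to 5.3%. The inflation therefore comes from the filter.

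**4. Would adjusting for the pre-randomisation score repair it?** A second null model was used for the NRS. Assumptions: mean 6.5–7, between-patient SD 1.0–1.2, measurement SD 0.8–1.2, monthly fluctuation SD 0.7, common improvement 0–0.5. The >20% rule favours patients whose first score was high by chance, so Group A starts about 0.4–0.8 points worse on it. Adjusting for that score widens the spurious T1 difference from about 0.5–0.8 to 0.8–1.1 points, and raises false positives from about 14–45% to 37–82%. Adjustment makes matters worse. This model yields fewer responders (roughly 13–32%) than the quota of 20 from about 45 needs, so it is used here for the direction of the covariate's effect only.

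**The case against.** **A response run-in has a rationale.** Section 3.7 describes Sativex as indicated for patients who improve in a four-week initial trial. That explains why responders are of interest. It does not make them comparable with controls who passed no such filter.

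**It is a pilot with no formal hypothesis, and section 3.1 does not use the word randomised.** Both are true, and both lower the weight of false-positive rates. But sections 3.5 and 4 do present the comparison as randomised, and the pilot is meant to feed a later trial.

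**The planned tests are not the ones simulated.** This stands in part. Section 3.13 tests clinical scales within group and leaves NRS off its list. The stated A-versus-B test is the rmANOVA on TMS measures from a hand muscle, whose correlation with one-month response is not given and may be low. At r = 0.2 the inflation is only to 7–8%. The figures are illustrations, not estimates for this trial.

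**Stronger readings that the text does not support.** A reader might infer that the design is bound to favour Sativex. The direction for change scores depends on whether T0 precedes or follows the run-in, which is not made fully clear. If T0 follows it, Group A was chosen on a favourable score and regression to the mean would work against Sativex. A reader might also infer from the Abstract that Group B are Sativex failures. The Abstract does not say so, and sections 3.2 and 3.4 point the other way.

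**Conclusion.** The point holds on structure alone and rests on no assumed number. Randomisation covers the 90 patients at prescreening. The 40-patient comparison sets Sativex responders against controls and is not randomised. The two definitions of Group B contradict each other and must be reconciled.

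The size of the resulting bias cannot be derived from the documents. For r between 0.2 and 0.7 and a responder share of 44% to 50%, with no drug effect, type I error at a nominal 5% is about 7% to 54% against unselected controls, and about 16% to 99% if Group B is non-responders from the control arm. The documents do not support a single figure or a fixed direction for change scores.

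**What to change.** **If the 40 are already selected** (section 3.4 is in the past tense):

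- State in 3.5 and 4 that randomisation applies to the 90-patient prescreening stage only.
- Call the 40-patient analysis a non-randomised comparison of Sativex responders with controls.
- Report how many were randomised to Sativex and how many of them responded.
- Limit the conclusion, and any use of the estimates in planning a confirmatory trial, accordingly.

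**In either case:** reconcile the Abstract with 3.2 and 3.4 to one definition of Group B, take Group B consecutively from the randomised control arm, and name the scale in the >20% rule (MRS appears only in that rule; the scale listed elsewhere is NRS). State whether T0 precedes or follows the run-in. Do not offer adjustment for the pre-randomisation spasticity score as a remedy.

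**If selection is still open and a randomised effect is the aim:** carry forward the first 20 of each arm in randomisation order, analyse them as randomised, and show responders as a labelled subgroup.

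**Cost.** The first route is wording and one reported fraction, at the price of a weaker claim. The last adds no analysed patients, but non-responders dilute the contrast and the question is no longer about responders only. The dilution cannot be quantified because no response rate is given.
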